#### **8.4.2. Standard insulin therapy with CGM (control)**

This session will be conducted by a pump educator and/or member of the study team. This visit can be done at the clinical research facility or outpatient department. Study training, where preferred, will be supported by online training modules and webinars developed for the CGM system.

Participants will receive training to cover key aspects of the study CGM device. Particular attention will be paid to:

- Insertion and initiation of sensor session

- Interpreting real-time CGM data and trend arrows
- The impact of diet and lifestyle on glucose sensor readings and trends
- Setting and adjustment of alarms/alerts
- Managing hypo- and hyperglycaemia

Written easy to use guidelines for the operation of the CGM device will be provided. Competency on the use of CGM will be assessed by the study team. Only participants who demonstrate competency on use of the CGM will continue to the home study phase.

Standard insulin therapy with CGM will start once the training session is completed. Participants will be advised to use their usual insulin therapy with CGM over the next 26 weeks. Participants will be asked to contact the study team if they encounter any problems with the CGM system.

All non-insulin diabetes therapies will also be continued throughout the study period. Throughout the trial, participants and/or the clinical team are free to adjust diabetes therapy as per usual clinical practice.

## **8.5. Telephone/email contacts after initiation of treatment arm**

All participants will be contacted by email / telephone within 48 hours and at one week after initiation of the respective study arm. The purpose of this contact would be to troubleshoot any issues with the devices, and to record any adverse events, device deficiencies, and changes in insulin doses, other medical conditions and/or medication.

Thereafter, participants will be followed up through study contacts (telephone / email) at monthly intervals to record any adverse events, device deficiencies, changes in insulin doses, other medical conditions and/or medication.

## **8.6. Visit 4 – 3 month visit**

Participants will attend the research centre for Visit 4 approximately three months after Visit 3. Participants will have a blood test for HbA1c, fasted lipid profile, renal function and liver function. Participant's weight, waist hip ratio and BP will be recorded and urine ACR measured. Participants will be asked to complete questionnaires to assess quality of life and diabetes management.

## **8.7. Visit 5 – End of study visit**

The participant will attend the research centre approximately six months after Visit 3. This will be the end of study visit. Participants will have a blood test for HbA1c, fasted lipid profile, renal function and liver function. Participant's weight, waist hip ratio and BP will be recorded and urine ACR measured. Participants will be asked to complete questionnaires to assess quality of life and diabetes management.

At the end of study visit, study devices will be collected and participants will resume their usual diabetes care.

A subset of participants will be invited to take part in a qualitative interview to assess quality-of-life impacts of using the closed-loop system.

## **8.8. Participant withdrawal criteria**

The following pre-randomisation withdrawal criterion will apply:

1. Participant is unable to demonstrate safe application of insulin therapy as judged by the investigator.

The following pre- and post-randomisation withdrawal criteria will apply:

2. Participant is unable to demonstrate safe use of insulin injections or study insulin pump, CGM and/or closed-loop during post randomisation training period as judged by the investigator.
3. Participants may terminate participation in the study at any time without necessarily giving a reason and without any personal disadvantage
4. Significant protocol violation or non-compliance
5. Recurrent severe hypoglycaemia events related to the use of the closed-loop system
6. Recurrent severe persistent hyperglycaemia events/DKA unrelated to infusion site failure and related to use of the closed-loop system
7. Decision by the investigator or the Sponsor that termination is in the participant's best medical interest
8. Allergic reaction to insulin, or severe reaction to adhesive surface of infusion set or glucose sensor

Participants who are withdrawn for reasons stated in (2) to (8) will be invited to provide a blood sample and complete questionnaires at the end of the planned study intervention.

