| End of study assessments                              | Weight, waist hip ratio and blood pressure will be measured and a blood sample will be taken for measurement of HbA1c, fasted lipid profile, renal and liver function. Urinary ACR will be measured. Human factors questionnaires will be completed and a subset of participants will participate in an interview study. Study devices will be returned and participants will resume their usual insulin therapy and standard glucose monitoring.                                                                                    |
| Procedures for safety monitoring during trial         | 
Standard operating procedures for monitoring and reporting of all adverse events and adverse device events will be in place, including serious adverse events (SAE), serious adverse device effects (SADE) and specific adverse events (AE) such as severe hypoglycaemia.
 
A data safety and monitoring board (DSMB) will be informed of all serious adverse events and any unanticipated serious adverse device effects that occur during the study and will review compiled adverse event data at periodic intervals.
 |
| Criteria for withdrawal of patients on safety grounds | 
A participant may terminate participation in the study at any time without necessarily giving a reason and without any personal disadvantage. An investigator can stop the participation of a participant after consideration of the benefit/risk ratio. Possible reasons are:
 
 
1. Participant is unable to demonstrate safe use of study devices as judged by the investigator
 
                                                                                              |

2. Serious adverse events
3. Significant protocol violation or non-compliance
4. Decision by the investigator, or the Sponsor, that termination is in the participant's best medical interest
5. Pregnancy, planned pregnancy, or breast feeding
6. Allergic reaction to insulin or severe allergic reaction to adhesive surface of infusion set or glucose sensor
7. Technical grounds (e.g. participant relocates)

Efforts will be made to retain participants in follow up for the final primary outcome assessment even if the intervention is discontinued, unless the investigator believes that it will be harmful for the participant to continue in the trial.

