## **8.4. Visit 3 - Training and initiation of the study devices**

### **8.4.1. Closed-loop (intervention)**

This session will be conducted by a pump educator and/or member of the study team. This visit can be done at the clinical research facility or outpatient department. Study training, where preferred,

can be supported by online training modules and webinars which have been developed for the closed-loop system.

Participants will receive training to cover key aspects of insulin pump use, CGM and closed-loop insulin delivery. Particular attention will be paid to:

- Insulin cartridge and infusion set changes and correct priming procedure
- Insertion and initiation of sensor session
- The impact of diet and lifestyle on glucose sensor readings and trends
- Hypo- and hyperglycaemia management
- Setting and adjustment of alarms/alerts
- Connection and disconnection of the closed-loop system

Written easy to use guidelines for the operation of the insulin pump, CGM and closed-loop system will be provided. Competency in the use of study pump, CGM and closed-loop system will be assessed by the study team. Only participants who demonstrate competency in use of the system will be allowed to continue to the home study phase.

Closed-loop glucose control will start once the training session is completed. Participants will be advised to continue closed-loop over the next 26 weeks. Participants will be asked to contact the study team if they encounter any problems with the closed-loop system.

All non-insulin diabetes therapies will be continued throughout the study period. Throughout the trial, participants and/or the clinical team are free to adjust diabetes therapy as per usual clinical practice.

A subset of participants (n=30, recruited from across UK sites) randomised to the closed-loop group will be invited to take part in a qualitative interview to explore their experiences of using the closed-loop system. These interviews will take place near the end of their participation in the trial.

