### **10.2. Recording and reporting of adverse events, serious adverse events and device deficiencies**

#### **10.2.1. Monitoring period of adverse events**

The period during which adverse events will be reported is defined as the period from the beginning of the study (obtaining informed consent) until 2 weeks after the end of the study participation (completion of the final study visit). Adverse events that continue after the participant’s discontinuation or completion of the study will be followed until their medical outcome is determined or until no further change in the condition is expected. The follow up of AEs may therefore extend after the end of the clinical investigation; however no new AEs will be reported after the trial reporting period.

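### Minor, cheap to fix: Section 8.8 gives withdrawn participants no safety contacts, and Section 10.2.1 leaves unclear when their adverse-event reporting ends

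*Protocol*

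**What the plan says.** - **Follow-up after withdrawal.** Section 8.8 states that participants withdrawn for reasons 2 to 8 "will be invited to provide a blood sample and complete questionnaires at the end of the planned study intervention". It names no other follow-up.
- **Retention.** The synopsis states: "Efforts will be made to retain participants in follow up for the final primary outcome assessment even if the intervention is discontinued". It excepts cases where the investigator believes that continuing would be harmful. The stated purpose is the primary outcome; safety is not mentioned.
- **Reporting period.** In Section 10.2.1, adverse events are reported from consent "until 2 weeks after the end of the study participation (completion of the final study visit"). Events that continue after the participant's "discontinuation or completion of the study will be followed until their medical outcome is determined" or no further change is expected. New events after the reporting period are not reported.
- **Safety evaluation.** Section 9.2 covers severe hypoglycaemia and other adverse events over 26 weeks and includes participants who withdraw. Section 13.3 also includes drop-outs and withdrawals. It lists numbers of events, numbers of participants with an event, and adverse and serious adverse events per participant, by treatment group.
- **Withdrawal triggers.** Two of the criteria in Section 8.8 refer to the closed-loop system alone: "Recurrent severe hypoglycaemia events related to the use of the closed-loop system" (criterion 5) and "Recurrent severe persistent hyperglycaemia events/DKA unrelated to infusion site failure and related to use of the closed-loop system" (criterion 6). Criterion 2 acts at the training visit after randomisation. Section 8.4.1 says of the closed-loop arm: "Only participants who demonstrate competency in use of the system will be allowed to continue to the home study phase". Section 8.4.2 sets a similar requirement for controls, limited to the glucose sensor.

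**The concern.** The protocol counts withdrawn participants in a 26-week safety evaluation but does not make sites keep asking them about events. A site that follows Section 8.8 to the letter makes at most one further contact, at week 26, for blood and questionnaires. Events after withdrawal are then either not recorded or recalled at that single optional contact.

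This is a rule about data collection, so the analysis plan cannot repair it. An event that nobody asked about cannot be recovered. Counts and per-participant numbers depend on how long each person was observed, so they fall when observation is cut short. The question is of some weight here because Section 13.11 justifies part of the increase from 96 to 224 participants by a stronger safety assessment.

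**Working it through.** **1. Two readings of the end of reporting.** Section 10.2.1 ends reporting 2 weeks after the end of study participation.

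- *Early reading: participation ends at withdrawal.* The synopsis uses the word in this sense: "An investigator can stop the participation of a participant after consideration of the benefit/risk ratio". Section 10.2.1 also sets discontinuation beside completion when it deals with continuing events, and Section 15 refers to using data obtained before withdrawal.
- *Late reading: participation ends at the final visit.* The parenthesis in Section 10.2.1 says so. A withdrawn participant who accepts the week-26 invitation could be treated as having such a visit, and Section 10.2.2 has adverse events elicited at every visit.

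A withdrawn participant who does not attend at week 26 has no final visit to which the parenthesis could apply. Section 8.5 describes the monthly contacts for participants generally. It neither excludes withdrawn participants nor says that their contacts continue.

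**2. Loss per withdrawn participant.** The inputs are the 26-week evaluation (Section 9.2) and the 2-week tail (Section 10.2.1).

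- Late reading, with the week-26 contact accepted and events asked about there: close to zero, subject to recall.
- Early reading, withdrawal at week w: max(0, 26 − (w + 2))/26 = max(0, 24 − w)/26.

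| Week of withdrawal | Share of 26 weeks not reported, early reading |
|---|---|
| 0 (training visit) | 24/26 = 92% |
| 12 | 12/26 = 46% |
| 20 | 4/26 = 15% |
| 24 or later | 0 |

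If withdrawals are spread evenly over weeks 0 to 26 (assumed), the mean share is (24²/2)/26/26 = 288/676 = 0.426.

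**3. Upper illustration for the whole trial.** Section 13.11 gives 224 participants and 20% dropout. Suppose that every dropout were a withdrawal of this kind and that the early reading applied.

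- Withdrawn: 0.20 × 224 = 44.8. Planned follow-up: 224 × 26 = 5,824 person-weeks.
- Spread evenly: 0.20 × 0.426 = 8.5%, about 496 person-weeks.
- All at week 20: 44.8 × 4/5,824 = 3.1%. All at week 0: 44.8 × 24/5,824 = 18.5%.
- At 10% or 30% withdrawal, spread evenly: 4.3% or 12.8%.

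Under the late reading with the contact accepted, each of these figures drops to near zero. They also include people who withdraw consent, whom no change of wording can reach.

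**4. Criterion 5 alone.** The protocol gives no severe hypoglycaemia rate for this trial. At an assumed 0.2 episodes per patient-year, an arm of 112 expects 112 × 0.5 × 0.2 = 11.2 events in 26 weeks. If counting stops 2 weeks after a second event and the personal rate is constant, the loss is about 112 × (0.2 × 24/52)³/6 = 0.015 events. By simulation with rates that vary between people (gamma-distributed, assumed), it is up to 0.40 events. The number of participants with any severe episode does not change, because the criterion acts only after a recurrence.

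**5. Sample size.** A difference of 0.8, SD of 1.2, two-sided 5% and 90% power give 48 per group, as Section 13.11 states. Nothing in this point changes that figure or the power.

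**The case against.** The strongest reply is that Section 10.2.1 defines its own term. The parenthesis names a visit as the end of participation, and Section 8.8 invites withdrawn participants back at the planned end, where events can be asked about. The synopsis already separates stopping the intervention from leaving follow-up, and Section 8.5 excludes nobody. Counting withdrawals in the safety evaluation means that their data are used; it does not promise 26 observed weeks for each of them. The only planned safety comparison is of severe hypoglycaemia rates, if there are enough events, and person-time rates are little affected.

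Much of this stands. The late reading is available, the two sets of sections do not formally contradict each other, and the loss may be near zero for those who return. What it does not answer is that attendance at week 26 is by invitation, that no section tells sites to ask about adverse events between withdrawal and that date, and that one recall after several months is weaker than monthly questions.

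A reader might go further and infer a bias in favour of closed-loop, because criteria 5 and 6 name only that system and its training is more demanding. The documents do not support that step. They give no withdrawal rates by arm, criterion 7 and the synopsis reason of serious adverse events apply to either arm, and in an open-label trial controls could leave as often or more often. Any ratio of events between arms would rest on invented withdrawal rates.

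**Conclusion.** The point holds as a minor one. Section 8.8 secures no safety follow-up after withdrawal, and Section 10.2.1 does not say plainly when reporting ends for a withdrawn participant, so sites in seven countries may apply different rules.

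The loss per withdrawn participant lies between near zero and (24 − w)/26 of the reporting time. The 8.5% of planned person-weeks is an upper illustration. It assumes the early reading, even timing, and that the entire 20% dropout consists of such withdrawals; it is not an expected value. Withdrawal could differ between arms, but neither direction nor size of a bias is established. The primary endpoint and the gatekept tests are not affected.

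**What to change.** Leave the withdrawal criteria as they are and add the following to Sections 8.8 and 10.2.1:

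- For randomised participants, meeting criterion 2 or any of criteria 4 to 8 stops the device or allocated treatment, not safety follow-up.
- The monthly contacts in Section 8.5 continue in both arms and record severe hypoglycaemia, diabetic ketoacidosis and serious adverse events to planned week 26 plus 2 weeks.
- Exceptions: the participant withdraws consent; the investigator judges follow-up harmful, as the synopsis allows; or a country rule ends follow-up, as for pregnancy in Switzerland (Section 10.2.4.2) and Germany (Section 10.2.4.4).
- For these participants, the end of study participation in Section 10.2.1 is the planned week-26 date, whether or not a visit takes place.

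The cost is a few sentences of protocol wording and some extra calls to people who have stopped treatment. Non-serious events after withdrawal would still be incomplete, which seems an acceptable price for keeping the calls short. Sample size and power do not change.

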## **8.9. Study stopping criteria**

The study may be stopped if three consecutive participants withdraw from the study for safety reasons, or on the advice of the independent Data Safety Monitoring Board (DSMB).

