#### **10.1.4. Serious Adverse Event**

A serious adverse event (SAE, ISO 14155, 3.45) is an adverse event that:

- led to a death
- led to a serious deterioration in the health of the participant, users, or other persons that either resulted in:
  - a life threatening illness or injury
  - a permanent impairment of a body structure or function including chronic diseases
  - in-patient hospitalisation or prolonged hospitalisation
  - medical or surgical intervention to prevent life-threatening illness or injury or permanent impairment to a body structure or a body function
- led to foetal distress, foetal death or a congenital abnormality or birth defect including physical or mental impairment

A planned hospitalisation for pre-existing condition, or a procedure required by the study protocol, without a serious deterioration in health, is not considered to be a serious adverse event.

More than one of the above criteria can be applicable to one event. Life-threatening in the definition of a serious adverse event or serious adverse reaction refers to an event in which the participant was at risk of death at the time of the event; it does not refer to an event which hypothetically might have caused death if it were more severe. Medical judgement should be exercised in deciding whether an adverse event or reaction is serious in other situations.

Important adverse events or reactions that are not immediately life-threatening or do not result in death or hospitalisation but may jeopardise the participant or may require intervention to prevent one of the other outcomes listed in the definition above, should also be considered serious.

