### **10.2.3. Severe hypoglycaemia**

Severe hypoglycaemia will be defined as an event requiring assistance of another person due to altered consciousness to actively administer carbohydrate, glucagon, or other resuscitative actions. This means that the participant is impaired cognitively to the point that he/she is unable to treat him or herself, is unable to verbalize his or her needs, is incoherent, disoriented, and/or combative, or experiences seizure or coma. If plasma glucose measurements are not available during such an event, neurological recovery attributable to the restoration of plasma glucose to normal is considered sufficient evidence that the event was induced by a low plasma glucose concentration.

Severe hypoglycaemia will be regarded as a foreseeable adverse event and an adverse event form will be completed. Severe hypoglycaemia is not necessarily a serious adverse event and hence may

not require immediate reporting to the Sponsor. Non-severe hypoglycaemia will not be reported or considered an adverse event.

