## **10.6. Data Safety Monitoring Board (DSMB)**

An independent Data Safety Monitoring Board (DSMB) will be informed of all serious adverse events and any unanticipated adverse device effects that occur during the study and will review compiled adverse event data at periodic intervals.

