### **13.9. Interim monitoring and analysis**

No formal interim analysis will be performed. Interim analyses of the safety data primarily will be performed at regular intervals (at least annually) for review by the DSMB. The DSMB members will comply with DSMB charter. The DSMB will be asked to give advice on whether the accumulated data from the trial, together with results from other relevant trials, justifies continuing recruitment of further participants or further follow-up.

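### The numeric stopping trigger in Protocol 8.9 counts an undefined run of three safety withdrawals and would seldom fire at low to moderate rates; the consequence is minor and the fix is cheap

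*Protocol*

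**What the plan says.** Section 8.9 has two limbs. The numeric one reads: "The study may be stopped if three consecutive participants withdraw from the study for safety reasons". The other is stopping on the advice of the independent DSMB.

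Section 8.8 puts all withdrawals in one list. Item 3 reads "Participants may terminate participation in the study at any time without necessarily giving a reason", and item 4 covers protocol violation and non-compliance. The closed-loop safety items are item 5, "Recurrent severe hypoglycaemia events related to the use of the closed-loop system", and item 6, its counterpart for hyperglycaemia and DKA. Items 2 (unsafe use of injections or devices found during training), 7 (best medical interest) and 8 (allergic or adhesive reactions) can arise in either arm.

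The synopsis adds: "Efforts will be made to retain participants in follow up for the final primary outcome assessment even if the intervention is discontinued".

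On oversight, sections 10.6 and 19.1 say that the DSMB hears of all SAEs and unanticipated adverse device effects, and 10.6 that it "will review compiled adverse event data at periodic intervals". Section 13.9 says that safety analyses "will be performed at regular intervals (at least annually) for review by the DSMB". Section 10.2.3 notes that "Severe hypoglycaemia is not necessarily a serious adverse event".

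**The concern.** A numeric trigger should respond when safety withdrawals accumulate. This one responds only when they fall next to each other in a sequence that the protocol does not define. It does not say whether order follows enrolment, randomisation or date of withdrawal, or whether the count runs by site, by arm or across the trial. It does not say which 8.8 items are safety reasons. The synopsis heading on withdrawal on safety grounds does not settle that, because its list also includes non-compliance and relocation.

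The trigger may also miss people. Someone who stops the device for safety but stays in follow-up, as the synopsis encourages, may not count as having withdrawn from the study.

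The gap that a numeric trigger could cover is narrow but real. A device-related safety discontinuation that is not an SAE, for example after some severe hypoglycaemia, need not reach the DSMB individually. Its guaranteed route is the compiled review, at least once a year.

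**Working it through.** **Inputs.** The protocol states no operating characteristic for 8.9, so there is no figure to reproduce. Section 13.11 gives 224 randomised, 112 per arm, and a 20% dropout allowance: 0.20 × 224 = 44.8, about 45 withdrawals. Half of that, 22, is taken as a lower case. Safety-withdrawal rates are assumptions: 2%, 5% and 8% of the 112 closed-loop participants, with 0% to 3% in control.

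**Formula, withdrawal order.** Place k safety withdrawals at random among n withdrawals. The number of arrangements with no run of three is the coefficient of x^k in (1 + x + x²)^(n−k+1). So P(run | k) = 1 − that coefficient / C(n, k). For k = 3 this reduces to (n − 2)/C(n, 3).

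**Hand check, three safety withdrawals:**
- no unrelated withdrawal among them (n = 3): 1/1 = 100%
- one unrelated (n = 4): 2/4 = 50%
- two (n = 5): 3/10 = 30%
- three (n = 6): 4/20 = 20%
- spread over all 45: 43/14,190 = 0.3%; over all 22: 20/1,540 = 1.3%

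**Whole trial.** Average P(run | k) over k, which is binomial(112, p) for closed-loop plus an independent binomial(112, q) for control.

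| Closed-loop p | Control q | Run, 45 withdrawals | Run, 22 withdrawals | Three or more closed-loop in total |
|---|---|---|---|---|
| 2% | 0 | 0.5% | 2% | 39% |
| 5% | 0 | 7% | 24% | 92% |
| 8% | 0 | 25% | 60% | 99% |
| 5% | 2% | 18% | 48% | 92% |
| 8% | 3% | 49% | 86% | 99% |

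The last column is P(Bin(112, p) ≥ 3). At p = 5% the expected number of closed-loop safety withdrawals is 112 × 0.05 = 5.6. The control-arm rows matter because 8.9 is not limited by arm: a control-arm safety withdrawal advances the run.

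**Enrolment order.** Every participant who does not withdraw for safety now breaks the run. With safety withdrawals at 5% of all 224 (about 11 expected), the chance of three in a row is 2.6%; at 2% it is 0.2%.

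**Within one year.** Section 22 runs from September 2024 to March 2027, about 30 months. Twelve of these, with even accrual, cover about 112 × 12/30 = 45 closed-loop participants and 45 × 12/30 = 18 withdrawals (9 in the lower case). At 5% closed-loop and none in control, the run occurs in 3% (18 withdrawals) or 10% (9), and a total of three in 39%. At 2% the total is reached in only 6%. The cumulative count is better than the run, but often silent within a year as well.

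**The case against.** The best case for leaving 8.9 alone is that little depends on it. It says that the study may be stopped, so nothing bars earlier action. The DSMB limb is independent of any count. SAEs and unanticipated adverse device effects reach the DSMB as they occur, and 10.1.4 counts as serious an event that "may jeopardise the participant or may require intervention to prevent one of the other outcomes listed in the definition above", which would take in many severe hypoglycaemia episodes. Annual review is a minimum, and the DSMB charter, which is not shown, may set shorter intervals or its own triggers. The rates are assumed, and the 45 is a sample-size allowance, not a forecast. A run also performs well when safety withdrawals cluster or dominate: if 40% to 50% of 45 withdrawals were for safety, it would occur in 86% to 97% of trials. All of this stands, and it is why the point is minor.

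A reader might infer that any control-arm withdrawal resets the count. The text does not support that: 8.9 speaks of participants without naming an arm, so only a non-safety withdrawal breaks a run counted by withdrawal order. A reader might also infer that the trial has no effective safety brake, or that a signal would wait a full year. Neither follows, given the DSMB limb, the individual SAE reports and the unseen charter.

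What the objection does not remove is that the one numeric criterion is order-dependent and undefined, and that no other section repairs it.

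**Conclusion.** The point holds as a minor one. The numeric limb of 8.9 is ambiguous and, at low to moderate rates, insensitive. At an assumed 5% closed-loop rate it is met in 7% to 24% of trials with no control-arm safety withdrawals, and in 18% to 48% with 2% in control, against 92% for a simple total of three. These figures assume withdrawals in random order and compare how often each signal occurs, not stopping with review. They include discontinuations for SAEs that the DSMB would already know of, so the practical gain from a better trigger is smaller than the contrast suggests.

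The exposure is confined to device-related safety discontinuations that are not SAEs. Neither the primary analysis nor the sample size is affected.

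**What to change.** Replace the consecutive run in 8.9 with wording such as:

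*An unscheduled DSMB review will be held once three closed-loop participants in total have permanently discontinued the device for a device-related safety reason (8.8 items 2, 5, 6 or 8 where related to the closed-loop system or its components, a device-related SAE, or an item 7 decision on safety grounds), whether or not they remain in follow-up.*

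Give the DSMB the control-arm safety-withdrawal count alongside, and keep DSMB advice as the route to stopping.

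The cost is this sentence, one CRF field for the reason for device discontinuation, and an occasional extra meeting. The chance of reaching three among 112 over the whole trial is about 10% at a true discontinuation rate of 1% and 39% at 2%. The change closes the gap only in part: a single non-serious severe hypoglycaemia episode without discontinuation would still wait for the compiled review.
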